#### Follow-up

Conferring to national guidelines follow-up will include imaging, laboratory tests including tumour markers (CEA) and clinical examination every 3 months for the first year and every 6 months hereafter. Follow-up cross-sectional imaging should include at least an abdominal ceCT or upper abdominal ceMRI at the given time-points. Participating centres are free to add ^18^F-FDG PET-CTs at specific time-points or to use alternating specific modalities, as long as the follow-up protocol is pre-approved by the trial coordinators and as long as follow-up imaging is identical for both treatment arms. Quality of life questionnaires will be assessed at baseline, every 3 months for the first year and every 6 months hereafter accordingly. Data will be collected in Castor EDC® [33], only available for related research investigators.

#### Primary and secondary objectives

The main objective is to prove non-inferiority of thermal ablation compared to hepatic resection in patients with at least one resectable and ablatable CRLM (≤3 cm) and no extrahepatic disease. Primary endpoint is OS. Main secondary endpoints are overall disease-free survival (DFS), time-to-progression (TTP), time-to-local-progression (TTLP), primary and assisted technique efficacy (PTE, ATE), procedural morbidity and mortality, length of hospital stay, assessment of pain and quality of life (QoL), cost-effectiveness ratio (ICER) and quality-adjusted life years (QALY).

Pain analysis will be performed using visual analogue scale questionnaires (VAS) assessed prior to, directly after and every 3 months after local treatment; administered pain medication will be registered. Quality of life analysis will be performed using European Organisation for Research and Treatment of Cancer Quality of Life questionnaires (EORTC-QLQ-CR29, EORCT QLQ-C30, EQ-5D) prior to, and every 3 months after local treatment. Patients who complete the quality-of life questionnaires at baseline and at least once during treatment and follow-up will be included in the analysis. The largest decrease in quality of life with respect to baseline will be calculated. The Wilcoxon rank sum test will be used to detect statistical differences between the two treatment arms.

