##### Cost analysis

the primary health outcome measure in this economic evaluation will be the total quality adjusted life years (QALY) per trial arm. QALYS will be calculated by using the utility scores linked to the various health states of the EQ-5D; in essence the length of time a patient spends in a particular health condition is weighed by the corresponding utility. Missing data on costs and utilities will be imputed using multiple imputation. The difference in total costs and total QALYs in both arms will be used to calculate the incremental cost-effectiveness ratio (ICER): the cost per QALY gained (or cost-savings per QALY gained or lost), using the formula: ICER = (Cintervention - Ccontrol)/(QALYintervention - QALYcontrol). Cost and health effect will be discounted using the Dutch discount rates of 1.5% for health effects and 4% for costs. In addition, to allow comparison with international studies, discount rates of 3% for both health effects and costs will be used as well. To assess the impact of uncertainty, a probabilistic sensitivity analysis will be performed using the non-parametric bootstrap with 5000 replications. The results will be presented on cost-effectiveness planes. In addition, ICER acceptability curves will be presented and univariate sensitivity analyses will be performed focusing on uncertainty around most important costs-items.

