In conclusion, a recently published systematic review and meta-analysis reported that further randomized assessments of thermal ablation with curative intent to current-day palliative chemotherapy alone should be considered unethical [36]. Therefore, the highest achievable evidence level for unresectable CRLM seems to be reached. According to above mentioned superior safety profile, lower complication-rate and competitive long term survival after thermal ablation for CRLM challenges liver surgery and fiats the setup of this randomized controlled trial. If thermal ablation for resectable CRLM proves to be non-inferior to surgery, a reduction of the post-procedural morbidity and mortality, length of hospital stay and incremental costs can be expected, with better quality of life and without compromising oncological outcome.

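### The first quality-of-life and EQ-5D form after treatment is at 3 months, so an arm difference that resolves earlier enters neither the QoL comparison nor the QALYs

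*Protocol article*

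**What the plan says.** Two sections of the protocol article give the QoL schedule.

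- Primary and secondary objectives lists the two EORTC forms and the EQ-5D, ending "EQ-5D) prior to, and every 3 months after local treatment".
- Follow-up says: "Quality of life questionnaires will be assessed at baseline, every 3 months for the first year and every 6 months hereafter accordingly".

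The two differ after the first year, but both put the first post-treatment form at month 3. Pain on the VAS is treated differently in the same paragraph, being "assessed prior to, directly after and every 3 months after local treatment".

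The QoL analysis is then fixed: "The largest decrease in quality of life with respect to baseline will be calculated". The arms are compared on this by a Wilcoxon rank sum test. The analysis set is also fixed: "Patients who complete the quality-of life questionnaires at baseline and at least once during treatment and follow-up will be included in the analysis". No form during treatment appears on either schedule.

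For the economic evaluation, Cost analysis defines QALYs from the EQ-5D: "the length of time a patient spends in a particular health condition is weighed by the corresponding utility". The Discussion, under Partial hepatectomy versus thermal ablation, states what the authors expect if ablation proves non-inferior: "a reduction of the post-procedural morbidity and mortality, length of hospital stay and incremental costs can be expected, with better quality of life".

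**The concern.** Any difference between resection and ablation in complications and recovery should be largest in the first weeks. The article's own background figures point that way: 40% complications after hepatic resection (Partial hepatectomy) against 6–9% after thermal ablation (Radiofrequency ablation). Its early window for reporting life-threatening or fatal serious adverse events is 90 days, about 13 weeks. The first post-treatment questionnaire falls due as that window closes.

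The QoL statistic aims at the lowest point after baseline, yet no form is scheduled where a procedural low would fall. The statistic will instead reflect whatever lowers QoL from month 3 on. For QALYs, the interval from baseline to month 3 is filled in from its two ends. Multiple imputation, which the article plans for missing costs and utilities, does not help. It fills in forms that were due and not returned, and has no observed early values from which to learn a dip that nobody was scheduled to report.

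At stake are the QoL comparison and the denominator of the ICER. The primary endpoint, overall survival, is untouched.

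**Working it through.** **No stated figure to reproduce.** The article gives no effect size, power or expected QALY difference for QoL or EQ-5D. Its sample size is for overall survival only and does not bear on this point.

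**Inputs from the article.** EQ-5D at baseline (before the procedure) and at weeks 13, 26, 39 and 52 in year 1.

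**Assumptions, not in the article.** Resection carries an extra utility loss d = 0.1 to 0.3 relative to ablation just after the procedure, recovering linearly to zero at week w. Randomisation makes the expected baseline difference zero. Values between forms are joined by straight lines.

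**True QALY difference.** Linear recovery: d × w / 2 / 52.
- d = 0.1, w = 4: 0.1 × 4 / 2 / 52 = 0.0038
- d = 0.3, w = 12: 0.3 × 12 / 2 / 52 = 0.0346

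A loss that stays flat and then ends would be twice this: 0.0077 to 0.0692. The upper end needs a loss of 0.3 held for 12 weeks and gone by week 13, so the linear range is the more reasonable guide.

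**Recorded by the planned schedule.** The difference at week 13 is d × (1 − 13/w), or zero if w ≤ 13. With zero at week 0 and again at week 26 (for w ≤ 26), the recorded area is 13 × d × (1 − 13/w) / 52.

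| Recovery w (weeks) | True, per unit d | Recorded, per unit d | Share recorded |
|---|---|---|---|
| 4 | 0.0385 | 0 | 0% |
| 12 | 0.1154 | 0 | 0% |
| 20 | 0.1923 | 0.0875 | 45% |
| 26 | 0.2500 | 0.1250 | 50% |

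The zero for w ≤ 13 does not depend on the straight-line rule. Neither scheduled value carries the dip, so no rule that fills in between them can show it. The same holds for the greatest fall from baseline.

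**Recorded with added forms at weeks 2 and 6.** For w = 12, per unit d, the differences are 0 (week 0), 0.833 (week 2), 0.5 (week 6) and 0 (week 13). The area is 2 × 0.833/2 + 4 × (0.833 + 0.5)/2 + 7 × 0.5/2 = 0.833 + 2.667 + 1.750 = 5.25 utility-weeks, against a true 6, or 88%. The same sum gives 75% for w = 4, 67% for w = 6, 91% for w = 8, 101% for w = 20 and 92% for w = 26.

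**The case against.** The strongest reply is that the loss is small, uncertain and partly covered elsewhere. Much of that stands.

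- **Recovery time.** No section says how long recovery takes. A reader might infer that the trial cannot see a QoL difference at all. That holds only if the difference has ended by month 3; under linear recovery over 20 to 26 weeks about half is recorded.
- **Laparotomy.** Under Inclusion, Randomization and Thermal ablation, patients outside the percutaneous or laparoscopic group are randomised during open surgery. Both arms share the incision, so its recovery cost largely cancels and the net difference is probably smaller there.
- **Early deaths.** A reader might infer that the missed dip is nearly the whole QALY difference. The cited 90-day mortality is 4% after resection and below 1% after ablation. Three percentage points over the 3-year horizon, at an assumed utility of 0.7 to 0.8 and assuming those patients would otherwise have lived all 3 years, give 0.03 × 3 × 0.7 = 0.063 to 0.03 × 3 × 0.8 = 0.072 QALY. Deaths count whatever the form dates, and this exceeds the whole linear range.
- **Noise in the ICER.** With 309 per arm and an assumed QALY SD of 0.3 to 0.7, the standard error of the difference is SD × √(2/309) = 0.024 to 0.056. Most of the missed range lies within about one standard error, so extra forms would not by themselves settle the ICER. The article already plans bootstrapping, cost-effectiveness planes and acceptability curves.
- **Other early records.** Pain directly after treatment, pain medication, procedural morbidity and length of stay are all collected. An early advantage would not go unnoticed.
- **Rationale.** The article lists better QoL beside lower morbidity and shorter stay. It does not say that one causes the other, nor place the gain in the first weeks; that link is a plausible inference.

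None of this removes the gap. The other early records enter neither the QoL comparison nor the utilities, and the schedule is stated outright in two sections, not left to a fuller document.

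**Conclusion.** The point holds in a limited form. An arm difference in QoL or utility that resolves before month 3 is absent from both the QoL statistic and the QALYs, and one that lasts longer is recorded only in part. Under an assumed net difference of 0.1 to 0.3 recovering linearly over 4 to 12 weeks, about 0.004 to 0.035 QALY is missed; both ranges are assumptions. If resection has the deeper early loss, the error runs against ablation.

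The documents do not support saying that the trial is bound to report no QoL difference, that this is most of the QALY difference, or that it alone makes the ICER uninformative. It is an inexpensive improvement to secondary objectives.

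**What to change.** Add the EQ-5D, the QLQ-C30 and the VAS for pain at one or two points in the first weeks after the procedure, for example at about 2 and 6 weeks. Use the same times in both arms and remote completion. Name these points in the QoL comparison and include them in the QALY area under the curve.

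For patients already treated, or if no points are added, state that the QoL and QALY results exclude recovery before 3 months.

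The cost is a short amendment, one or two further questionnaire rounds and slight patient burden; remote completion needs no clinic visit. Patients already treated will have no early values. The article reports treatment starting in two hospitals at the end of 2017, with numerous centres still awaiting local approval, so at that stage later patients could still have been covered.

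In the same amendment, reconcile Primary and secondary objectives (3-monthly throughout) with Follow-up (6-monthly after year 1).

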Additional unablatable CRLM should be resectable	Immunotherapy ≤6 weeks prior to the procedure
Maximum number of CRLM 10	Chemotherapy ≤6 weeks prior to the procedure
Resection for resectable lesions considered possible obtaining negative resection margins (R0) and preserving adequate liver reserve	Pregnant or breast-feeding subjects. Women of childbearing potential must have a negative pregnancy test performed within 7 days of the start of treatment
Resectability and ablatability should be re-confirmed by intra-operative ultrasound (IOUS) and full surgical exploration	Compromised liver function (e.g. signs of portal hypertension, INR > 1,5 without use of anticoagulants, ascites)
Eastern Cooperative Oncology Group status (ECOG) 0–2	Uncontrolled infections (> grade 2 NCI-CTC version 3.0)
American Society of Anesthesiologists (ASA) grade 1–3	Severe allergy to contrast media not controlled with premedication
Life expectancy of at least 12 weeks	Any condition that is unstable or that could jeopardize the safety of the subject and their compliance in the study;
Adequate bone marrow, liver, and renal function as assessed by local usual laboratory tests. As usual, these results should be judged by the local investigator and should be conducted within 7 days prior to definite inclusion. Written informed consent	Substance abuse, medical, psychological or social conditions

The total duration of the study is around 13 years considering an inclusion time of 3 years and a minimum follow-up period of 10 years. All participants will provide written informed consent.The flow diagram of is shown in Fig. 1.

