#### Sample size calculation and statistical considerations

We hypothesize (null-hypothesis) that thermal ablation is non-inferior to surgical resection for the selected patient groups in terms of the primary objective (OS). The Cox proportional hazards model (1-sided; non-inferiority or superiority) is used for sample size calculations (Table 3). Given the superior safety profile we consider a hazard ratio (HR) of 1.3 to represent the upper limit of non-inferiority (non-inferiority margin). An HR of 1.3 corresponds to a 56.5% chance of the ablated patients to die first ((P = HR/(1 + HR) = 1.3/(1 + 1.3) = 0.565 (56.5%)). We will have reached 60% of events (death) approximately 6.5 years after having included the last patient (overall probability of event, pE = 0.6). The calculated sample size therefore is 599 (NS). To account for a 10% drop-out ratio (NDO = 69) prior to randomization and a 3% loss to follow-up (NLTFU = 18) after randomization we need to recruit 687 patients (NI). A total number of 618 patients (687–69 (NDO)) will be randomized (NR) into one of two arms: arm A will undergo surgical resection (*n* = 309) and arm B thermal ablation (n = 309) for appointed target lesions.

**Table 3 Tab3:** Sample size calculation

Significance level (α)	0.05
Power (1-β)	0.80
Hazard Ratio (HR), θ (non-inferiority margin)	1.3
Null-Hypothesis Hazard Ratio, θ_0_	1.0
Recruitment time/study accrual (months)	36
Follow-up time (months)	60
Ratio control vs. experimental: m_2_/m_1_	1.0
Total sample size (N_S_)/total number to be randomized (N_R_)	599
Accounting for 3% loss to follow-up after randomization (N_LTFU_)	18
Accounting for 10% drop-out ratio pre-randomization (N_DO_)	69
Initial pre-randomization sample size – number of included patients (N_I_)	687

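### The quality-of-life test compares each patient's largest fall from baseline over an open-ended number of forms, so it depends on survival and form return and dilutes small to moderate early differences

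*Protocol article*

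**What the plan says.** All of this is in the protocol article.

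- **Measure** (Primary and secondary objectives): "The largest decrease in quality of life with respect to baseline will be calculated". No window is given.
- **Test** (same section): "The Wilcoxon rank sum test will be used to detect statistical differences between the two treatment arms". No allowance is made for the number of forms or the time observed.
- **Analysis set** (same section): "Patients who complete the quality-of life questionnaires at baseline and at least once during treatment and follow-up will be included in the analysis".
- **Schedule, first statement** (Follow-up): "Quality of life questionnaires will be assessed at baseline, every 3 months for the first year and every 6 months hereafter accordingly".
- **Schedule, second statement** (Primary and secondary objectives): "prior to, and every 3 months after local treatment", with no change of interval after year 1.
- **Length of follow-up** (Design): "considering an inclusion time of 3 years and a minimum follow-up period of 10 years". Table 3 lists 60 months. Neither is named as the window for quality of life.
- **Other use of the data** (Cost-effectiveness analysis): EQ-5D utilities are weighted by time to give QALYs over a 3-year horizon.

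**The concern.** The largest fall is an extreme value. A patient with one later form and a patient with twenty enter the same rank test, yet the second will show the larger fall by chance alone. The number of forms is set after randomization, by survival and by compliance. Survival is the primary endpoint, and the design accepts a hazard ratio of up to 1.3, so equal exposure in the two arms cannot be presumed.

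The measure also pools the recovery period with years of later forms. A less invasive procedure would most plausibly differ early, and the article's Discussion expects better quality of life if ablation is non-inferior. A maximum over many later forms dilutes that early signal. The trial could therefore miss a real early benefit, or report a difference that reflects only unequal follow-up.

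**Working it through.** The plan gives no figure for the quality-of-life analysis, so there is none to reproduce.

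**1. Number of forms.** Under the Follow-up section: 4 in year 1, then 2 a year for 9 years, 4 + 18 = 22 by 10 years. Under Primary and secondary objectives: 4 × 10 = 40. By 60 months the counts are 4 + 8 = 12 and 4 × 5 = 20.

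**2. Growth of the maximum with no true change.** Assumptions not in the documents: normal scores, SD 20, equal within-patient correlation ρ of 0.5 or 0.7. The fall at each form is the baseline deviation minus that form's deviation, so the expected maximum over k forms is 20 × √(1 − ρ) × m(k). Here m(k) is the expected maximum of k standard normals, and 20 × √(1 − ρ) is 14.14 or 10.95.

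| k | m(k) | ρ = 0.5 | ρ = 0.7 |
|---|---|---|---|
| 1 | 0 | 0 | 0 |
| 4 | 1.03 | 14.6 | 11.3 |
| 8 | 1.42 | 20.1 | 15.6 |
| 22 | 1.91 | 27.0 | 20.9 |
| 40 | 2.16 | 30.5 | 23.7 |

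**3. Unequal survival, no quality-of-life difference.** The sample size section gives "overall probability of event, pE = 0.6" about 6.5 years (78 months) after the last inclusion. Mean follow-up is then 78 + 36/2 = 96 months, and an exponential control hazard is −ln(0.4)/96 = 0.00954 per month. Simulation: 500 trials per setting, 300 per arm, both schedules, both correlations, forms missing only through death or end of follow-up, two-sided 5% test. With equal survival the test rejects in about 5% of trials. At HR 1.3 against ablation, mean forms per patient are 12.2 versus 11.1 (first schedule) or 21.0 versus 18.8 (second). The results depend on whether scores fall in the last 6 months of life:

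| Fall before death | Apparent advantage of the shorter-lived arm (points) | Rejection |
|---|---|---|
| none | +0.6 to +1.1 | 9–12%, nearly always in its favour |
| 10 | +0.3 to +0.6 | 5–8% |
| 20 | −0.1 to −0.4 | 4–6% |
| 30 | −0.8 to −1.3 | 8–19%, nearly always against it |

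Other runs of the first row gave 7–8%, so the overall range is about 7–12%.

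**4. Early difference, equal survival.** A dip at month 3 in the resection arm only:

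| Dip | Largest fall | Month-3 change, same test |
|---|---|---|
| 5 | 8–10% | 83–98% |
| 10 | 19–45% | about 100% |
| 20 | 85–100% | about 100% |

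Across further runs of this kind, power for the largest fall was about 8–12% for 5 points and 19–63% for 10. Adding a 20-point fall before death cuts the 10-point figure to 12–27%.

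Hand check of the month-3 column for 5 points: the SD of change is 20 × √(2(1 − ρ)) = 20 or 15.5, and the standard error is SD × √(2/300) = 1.63 or 1.26. Then 5/SE = 3.06 or 3.95; times √(3/π) = 0.977 gives 2.99 or 3.86. Subtracting 1.96 leaves 1.03 or 1.90, which is power of about 85% or 97%.

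**5. Sensitivity to the SD.** Power depends only on dip divided by SD. The rows in step 4 are 0.25, 0.5 and 1 SD and can be read that way for any other SD.

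**The case against.** **The direction of bias.** A reader might infer that the measure favours the arm that dies sooner. That holds only if scores do not fall before death. A fall of about 20 points in the last 6 months cancels the effect at HR 1.3, and 30 points reverses it. The documents give no figure that settles this. With equal survival and equal form return there is no bias, so the plan cannot be called biased without that condition.

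**Its size.** At the non-inferiority margin the shift is about 1 point or less. Much higher rejection rates appear at larger hazard ratios (42–57% at 2.0). The only such value in the article, 1.92, is pooled from observational RFA comparisons, and the Background warns of selection bias in comparisons of that kind.

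**Early differences.** A reader might infer that any early difference is buried. A 20-point dip is still found in 85–100% of trials. The month-3 comparator is also favoured by construction, because the dip was placed at the visit tested, and the recommended longitudinal model was not itself simulated.

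**Other measures.** EQ-5D feeds the QALYs, with multiple imputation, and pain, morbidity and length of stay also reflect early burden. This is fair, but none of them replaces the between-arm test on the quality-of-life questionnaires.

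**Left to the analysis plan.** Windows, missing forms and deaths are often specified there, and their absence here is not the point. The summary measure and test are stated outright, and added detail would not make a maximum over unequal numbers of forms comparable.

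**The schedule.** The second statement may only abbreviate the first. Even so, for a maximum the interval changes the endpoint, so the text needs to be settled.

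**Conclusion.** The concern holds in a limited form. The stated measure depends on how many forms each patient completes. If survival or form return differs between arms, the test can be biased in a direction that cannot be predicted: about 7–12% rejection at HR 1.3 with no quality-of-life effect and no decline before death, and nil or reversed with a marked decline.

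The firmer cost is power for small to moderate early differences, about 8–12% at 0.25 SD and 19–63% at 0.5 SD, where a month-3 comparison reaches 83–98% and about 100%. These figures rest on assumed normal scores, correlation 0.5–0.7, exponential survival and a dip centred on month 3. The growth of the maximum with the number of forms, and the 22-versus-40 discrepancy, need no assumption about SD or survival.

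**What to change.** 1. Make the main quality-of-life comparison a longitudinal model of score on arm, visit, arm-by-visit and baseline, with prespecified contrasts at month 3 and over year 1. The two schedule statements agree in year 1, so these contrasts do not depend on which one stands. Early contrasts also limit the influence of death: under the control hazard above, 1 − exp(−0.00954 × 3) = 2.8% have died by month 3 and 1 − exp(−0.00954 × 12) = 10.8% by month 12.
2. Keep the largest fall, if at all, as a descriptive measure over a fixed first-year window, shown with the number of forms completed per arm.
3. Reconcile the questionnaire schedules in the Follow-up and Primary and secondary objectives sections.

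The cost is analysis wording and one corrected sentence. The same questionnaires are used, and the sample size and primary analysis are untouched.

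### Quality of life is compared on each patient's largest decrease with no time window, so the result depends on how many forms are returned and on late disease, and small or short early differences are largely lost

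*Protocol article*

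**What the plan says.** All places are in the protocol article.

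- **Measure and test** (Primary and secondary objectives): "The largest decrease in quality of life with respect to baseline will be calculated", and "The Wilcoxon rank sum test will be used to detect statistical differences between the two treatment arms". No time window is attached.
- **Who enters** (same section): "Patients who complete the quality-of life questionnaires at baseline and at least once during treatment and follow-up will be included in the analysis".
- **Schedule, first statement** (Follow-up): "Quality of life questionnaires will be assessed at baseline, every 3 months for the first year and every 6 months hereafter accordingly".
- **Schedule, second statement** (Primary and secondary objectives): the sentence naming the questionnaires ends, and the next begins, "prior to, and every 3 months after local treatment. Patients who complete". No change after year 1 is mentioned.
- **Length of follow-up** (Design): "an inclusion time of 3 years and a minimum follow-up period of 10 years".
- **Deaths expected** (Sample size calculation and statistical considerations): "We will have reached 60% of events (death) approximately 6.5 years after having included the last patient".

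Quality of life is listed among the main secondary endpoints, and the end of the Discussion names its improvement as an expected benefit if ablation proves non-inferior. The only other stated use of these questionnaires is EQ-5D in the QALY calculation (Cost-effectiveness analysis).

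**The concern.** The largest decrease is the minimum of a patient's later scores, less baseline. Two features make it a poor basis for comparing resection with ablation.

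1. **It depends on the number of forms.** A minimum over more noisy scores is lower, even when nothing has changed. A patient with one form and a patient with 22 are ranked together as if their values were comparable. If one arm returns more forms, that arm looks worse.
2. **It has no window.** Forms continue through long follow-up in a population where most are expected to die. For many patients the worst form will be one near progression or death, which says little about recovery from the procedure.

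At stake is a stated benefit of ablation. Followed as written, the analysis can miss a modest difference after treatment, or show one that comes only from unequal form return.

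**Working it through.** **Inputs from the protocol.** The only power-based figure is for overall survival; none is given for quality of life. It reproduces: with one-sided α 0.05, power 0.80 and HR 1.3, events = 4 × (1.645 + 0.842)² / (ln 1.3)² ≈ 359.3, and 359.3 / 0.6 ≈ 599. Allowing for losses, 599 / 0.97 ≈ 618, or 309 per arm.

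Deaths: 60% at 6.5 years after the last inclusion is about 6.5 × 12 + 36 / 2 = 96 months for an average patient. Under exponential survival the median is 96 × 0.693 / 0.916 ≈ 73 months, about 6 years.

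**Number of forms after baseline.**

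| Horizon | Follow-up section | Objectives section |
|---|---|---|
| 3 years | 4 + 2×2 = 8 | 3×4 = 12 |
| 5 years | 4 + 4×2 = 12 | 5×4 = 20 |
| 10 years | 4 + 9×2 = 22 | 10×4 = 40 |

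**Effect of the number of forms alone.** With no true change, score SD 1 and within-patient correlation ρ, the expected largest decrease over k forms is √(1 − ρ) × E[maximum of k standard normals]. At ρ = 0.6 this is 0 for one form, 0.65 SD for 4, 1.03 for 12, 1.21 for 22 and 1.36 for 40. The disagreement between the two schedules alone shifts the measure.

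**Power, points scale.** Assumed, not in the protocol: 0–100 scale, between-patient SD 15, within-patient SD 8–13, 85% completion, median survival 6 years, 25-point decline in the last 9 months of life. The schedule is that of the Follow-up section, with two-sided tests at 0.05. The total SD is √(15² + 8²) = 17.0 to √(15² + 13²) = 19.8, so 5 points is about 0.25–0.29 SD.

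| Loss in the resection arm | Largest decrease, 36 months | Largest decrease, 120 months | Baseline-adjusted month 3 |
|---|---|---|---|
| 5 points at month 3 only | about 6–17% | about 8% | about 86–99% |
| 5 points through year 1 | 65–93% (gradual late decline) | about 24%, or 30–51% with a gradual late decline | 88–99% |
| 10/7/5/3 points at months 3/6/9/12 | 76–97% | 38–48%, or 54–86% with a gradual late decline | – |

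**Power, SD scale.** A second set of assumptions: 300 per arm, correlation 0.5–0.7, 60% dead by 96 months, 20% of forms missing, and a drop of 0 or 1 SD in the last 12 months of life. A 0.3 SD difference at month 3 only is detected by the largest decrease with 7–16% power over 5 years and 8–11% over 10, against 85–99% for the month-3 change. With the late drop, only 13–19% of resection patients have their worst form at month 3 over 10 years, although the whole effect lies there.

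**False positives with no true difference.** Points scale: 85% v 70% return gives about 25–37%. SD scale: 20% v 35% missing gives 24–26%, equal return gives 4–6%, and the month-3 test stays at 4–7%.

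**Unequal survival (HR 1.3), no quality-of-life effect.** With no late decline the test rejects in 10–13% of trials, and the longer-living arm looks worse. With a gradual 25-point late decline it rejects in 4–8%, and the mean difference changes sign (+0.25 points at within-patient SD 8, −0.18 at SD 13).

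**The case against.** - **The low power depends on the scenario.** This stands. A reader might infer that any early difference would be hidden. The protocol gives no effect size, SD or duration to support that, and the fading 10/7/5/3-point loss is still found with 76–97% power at 36 months. On the SD scale, a month-3 difference of 1.0 SD keeps 94% power over 5 years and 79% over 10.
- **The false positives need unequal return.** This stands. Both arms share one schedule and patients are meant to stay unaware of their arm, so nothing in the protocol predicts unequal return. With equal return and survival the fault is lost power, not bias.
- **The longer-living arm need not look worse.** This stands. More forms push one way and late decline the other, so the direction is not fixed.
- **Measurement error is not the particular defect.** This stands. A reader might infer that a minimum of noisy scores is mostly noise. However, the minimum of several noisy scores varies less than a single one, and every change score subtracts a noisy baseline.
- **Ten years of forms is an inference.** This stands in part. No quality-of-life horizon is set: Table 3 uses 60 months and the economic analysis 3 years. An analysis plan might set a window, but the article defines the measure without one while forms continue through follow-up. Power for the month-3-only loss is already low at 36 months.
- **Other outcomes capture recovery.** VAS pain, morbidity, length of stay and QALYs do so in part. None replaces the between-arm test of the QLQ-C30 and CR29 scores.

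**Conclusion.** The concern holds, with limits. The article itself fixes this measure and test, so it is not a detail left for later. Under the stated assumptions, a 5-point loss confined to month 3 would be found in about one trial in twelve over 120 months, although a month-3 comparison of the same patients would nearly always find it. Effects that are larger or last through year 1 lose power to a degree that depends on the horizon and on how late decline behaves. Unequal form return can raise the false-positive rate several-fold, against the arm that returns more forms. Unequal survival can shift the comparison in either direction. The mechanism follows from the definition of the measure; the sizes are illustrations, because the protocol gives no quality-of-life SD, effect size or completion rate. The primary survival analysis is not affected.

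**What to change.** 1. Make the main between-arm analysis of the QLQ-C30 and CR29 scores a repeated-measures model on the scheduled scores, adjusted for the baseline score. Report arm differences with confidence intervals at pre-named times that include month 3 and month 12.
2. Add a year-1 average only as a supplement. For a month-3-only effect it has just 18–35% power at 0.3 SD and 41–76% at 0.5 SD.
3. State that the analysis describes patients while alive.
4. Keep the largest decrease as descriptive, or limit it to a fixed early window such as year 1.
5. Reconcile the questionnaire schedules in the Follow-up section and in Primary and secondary objectives.

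The cost is wording in the protocol and analysis plan; the same forms are used and no new data are collected. The downside is that the time points and the scales of main interest must be named in advance.
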